**Secondary outcomes**
•Change from baseline in the Eriksen Flanker task performance (reaction time and accuracy).•Change from baseline in N-Back task performance (d-prime and reaction time across all levels).

**2.5.10 Statistical analysis**

Pre- and post-intervention neuroimaging and cognitive outcomes will be compared using paired samples t-tests (or Wilcoxon signed-rank tests for non-normally distributed data). Mixed-effects linear regression models will be used to examine the longitudinal trajectory of outcome variables, adjusting for relevant covariates (age, sex, baseline physical activity, HbA1c, and medication use). The association between intervention-induced changes in neuroimaging metrics and changes in vascular, metabolic, and cognitive outcomes will be examined using partial correlations and multivariate regression. Effect sizes (Cohen’s d and partial η
^2^) will be reported for all primary outcomes.

## 3 Dissemination

The findings of this study will be disseminated through multiple channels targeting both scientific and public health audiences. Primary results from each phase will be submitted for publication in peer-reviewed, open-access journals indexed in Scopus, with preference for journals specializing in neuroimaging, integrative medicine, and geriatric health.

Conference presentations will be submitted to national and international meetings in the fields of neuroscience, yoga and integrative medicine, and diabetes research. Research summaries will be shared with the Indian Council of Medical Research through mandatory progress and final technical reports as stipulated under the ICMR Small Extramural Grant conditions.

## 4 Study status

The study has received approval from the Indian Council of Medical Research (ICMR) under the Small Extramural Grants scheme (Priority Area: NCD Risk Factors — Diabetes; Aging and Elderly Health). Approval from the Institutional Ethics Committee (IEC) of Kasturba Hospital, Manipal, was sought. Prospective registration with the Clinical Trials Registry — India (CTRI) is completed. Concurrent activities include finalizing the research team, procuring study equipment (accelerometers and an ultrasound machine), and preparing participant-facing study materials.

## 5 Discussion

The current protocol describes a comprehensive, three-phase investigation designed to characterize alterations in the vascular, structural, and functional brain networks associated with obesity and T2DM in elderly adults, and to evaluate the neuromodulatory potential of a validated, structured yoga intervention using multimodal MR neuroimaging. To our knowledge, this is the first study to employ a concurrent multi-sequence MRI protocol, encompassing T1-weighted VBM with CAT12 ROI segmentation, ExploreDTI-based white matter tractography, resting-state fMRI, and carotid Doppler ultrasonography, specifically in an elderly obese-diabetic population undergoing a structured yoga intervention.

The decision to adopt a three-phase sequential design reflects the complexity of the research question and the need to establish a robust methodological foundation before proceeding to the intervention. Phase 1 addresses the critical need for a detailed neurobiological characterization of the target population prior to any therapeutic application, providing both the baseline comparator data and the evidence base that informed the structure of the Phase 3 intervention. Phase 2 ensures that the yoga module delivered in Phase 3 is not only scientifically grounded but also culturally appropriate, practically feasible, and formally validated for safety and content, a step conspicuously absent in most existing yoga intervention trials, which have frequently relied on ad hoc or unstandardized practice regimens. Phase 3 then applies the validated module in a prospective pre-post design, enabling within-subject quantification of neuroplastic change across all imaging and cognitive domains characterized in Phase 1.

Several limitations of the present study design merit acknowledgment. The study population is drawn from a single tertiary hospital in coastal Karnataka, which may limit the generalisability of the findings to other regions of India and to populations with differing levels of yoga familiarity, dietary patterns, and genetic risk profiles for T2DM and obesity. Second, the 6-month intervention window, while among the longest in the yoga-neuroimaging literature, may be insufficient to detect macrostructural volumetric changes in highly atrophied regions; longer follow-up periods and multi-site designs should be incorporated in future work.

Notwithstanding these limitations, the present study addresses a genuinely underserved research priority. Elderly adults with obesity and T2DM represent one of the fastest-growing demographic segments in India and globally, yet they remain largely excluded from neuroimaging research and targeted yoga intervention trials alike. The multimodal, multi-phase design of this protocol, combining carotid vascular imaging, structural morphometry, white matter tractography, resting-state fMRI, and formal yoga module validation under a single framework, constitutes a methodologically rigorous and clinically meaningful contribution to the field. If the hypothesized neuroplastic and vascular benefits of structured yoga are confirmed, the validated module and accompanying evidence base generated by this study could be directly integrated into community-level NCD prevention programs, AYUSH clinical practice guidelines, and geriatric rehabilitation protocols across India.

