**Methods:**

This three-phase, prospective protocol will be conducted at Kasturba Hospital and the Center for Integrative Medicine and Research, Manipal Academy of Higher Education, Manipal, India. Phase 1 is a case-control study (n = 80; 40 obese-diabetic, 40 obese-non-diabetic; age 60–80 years) employing carotid Doppler ultrasonography, T1-weighted voxel-based morphometry and region-of-interest segmentation (SPM12/CAT12/AAL3), diffusion tensor imaging with ROI-based tractography (ExploreDTI), and resting-state fMRI (CONN toolbox), alongside the Eriksen Flanker and N-Back cognitive tasks. Phase 2 involves the systematic development and expert content-validation of a structured, AYUSH-compliant yoga module tailored for elderly obese-diabetic adults. Phase 3 applies the validated module in a 6-month pre-post intervention, with objective adherence monitoring via triaxial accelerometry and repeat of the full Phase 1 neuroimaging and cognitive battery.

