**Discussion:**

This protocol addresses a critical gap in the yoga-neuroimaging literature by providing a multimodal, multi-phase framework to characterize neurovascular disease burden and evaluate structured yoga as a neurobiologically informed lifestyle intervention in a high-risk elderly population. Findings will inform AYUSH clinical guidelines, geriatric NCD prevention programs, and future randomized controlled trials.

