## 1. Introduction

The global burden of non-communicable diseases (NCDs) has reached unprecedented levels, with obesity and type 2 diabetes mellitus (T2DM) constituting two of the most consequential metabolic disorders of the twenty-first century. According to the World Health Organization, the worldwide prevalence of obesity has nearly doubled since 1990, with more than 890 million adults classified as obese in 2022.
^
1
^ Concurrently, the International Diabetes Federation estimates that approximately 537 million adults were living with diabetes in 2021, a figure projected to rise to 783 million by 2045.
^
2
^ These epidemiological trends are particularly alarming in the elderly population, among whom both conditions frequently co-occur and exert synergistic deleterious effects on systemic health. In India, rapid urbanization, sedentary lifestyles, and dietary transitions have accelerated the prevalence of these metabolic comorbidities, making them priority targets under the National Program for Prevention and Control of Cancer, Diabetes, Cardiovascular Diseases, and Stroke.
^
3
^

Beyond their well-established cardiovascular and metabolic sequelae, obesity and T2DM exert profound adverse effects on brain structure and function. Structural neuroimaging studies have consistently demonstrated accelerated brain atrophy, reduced grey matter volume, and compromised white matter integrity in individuals with obesity and T2DM relative to metabolically healthy controls.
^
4,
5
^ Particularly vulnerable regions include the hippocampus, prefrontal cortex, and parietal association areas, structures critically involved in memory consolidation, executive function, and visuospatial processing.
^
6
^ Diffusion tensor imaging (DTI) studies further reveal microstructural white matter disruption, evidenced by reduced fractional anisotropy (FA) and elevated mean diffusivity (MD) in major fiber tracts, consistent with demyelination and axonal loss.
^
7
^ These neuroanatomical alterations are accompanied by functional connectivity changes detectable on resting-state functional MRI, pointing to disrupted default mode and frontoparietal networks in metabolically compromised individuals.
^
8
^ Taken together, this body of evidence positions obesity associated T2DM as a significant and modifiable risk factor for accelerated neurocognitive aging.

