**2.3.1 Objectives**

The primary objective of Phase 1 is to determine and compare vascular, structural, and functional brain changes, along with alterations in cognitive function, between obese elderly adults with T2DM and those without T2DM using multimodal MR neuroimaging.

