**2.3.3 Inclusion criteria**
•Age 60–80 years, both sexes.•Clinical diagnosis of type 2 diabetes mellitus for the obese-diabetic group.•Body mass index (BMI) ≥ 25 kg/m
^2^ as per Asia-Pacific guidelines for obesity classification.
^
25
^
•Able to provide written informed consent independently or through a legally authorized representative.

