**2.3.5 Sample size**

Sample size was estimated using G*Power 3.1 software. A multivariate analysis of variance (MANOVA) power analysis was performed with an assumed medium effect size (f
^2^ = 0.25), a significance level of α = 0.05, and a desired statistical power of 0.80. This yielded a minimum total sample of 80 participants. Accounting for anticipated attrition and protocol deviations, 40 participants will be recruited to each group (obese-diabetic and obese-non-diabetic), yielding a total of 80 participants for Phase 1.

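### The Discussion's stated purpose goes beyond the design: with both groups obese and no non-obese reference, only the T2DM difference within obesity can be estimated

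*Protocol article*

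**What the plan says.** The article states its purpose at two different widths.

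- **Broad.** Section 5 (Discussion) presents the three-phase investigation as "designed to characterize alterations in the vascular, structural, and functional brain networks associated with obesity and T2DM in elderly adults". The Discussion paragraph of the Abstract says the framework will "characterize neurovascular disease burden".
- **Narrow.** Section 2.3.1 sets the Phase 1 comparison as one "between obese elderly adults with T2DM and those without T2DM using multimodal MR neuroimaging".

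The design follows the narrow version. The Abstract gives the groups as "n = 80; 40 obese-diabetic, 40 obese-non-diabetic; age 60–80 years". Section 2.3.5 repeats this: "40 participants will be recruited to each group (obese-diabetic and obese-non-diabetic), yielding a total of 80 participants for Phase 1". Section 2.3.3 applies the criterion "Body mass index (BMI) ≥ 25 kg/m" (squared) to everyone. Section 2.3.6.7 compares the two groups with t-tests or Mann-Whitney tests. It also plans regressions adjusted for age, sex, education and physical activity.

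The Introduction describes the expected damage as seen "in individuals with obesity and T2DM relative to metabolically healthy controls". The limitations in Section 5 name the single site and the six-month window. They do not mention that the study has no non-obese reference.

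**The concern.** A reader of the Discussion or Abstract will expect the study to say something about obesity and about the two conditions together. The between-group comparison cannot do that, because all participants are above the obesity threshold.

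Two misreadings become easy:

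- **A small or null difference** could be taken to mean that the brains of obese-diabetic adults are little affected, when both groups may be affected.
- **A clear difference** could be reported as the effect of obesity plus diabetes, when it is the difference that goes with diabetes among people who are already obese.

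The article intends its findings to feed clinical guidelines and prevention programmes, so an overbroad reading could travel beyond the paper.

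A smaller matter concerns the regressions. The groups may differ in how obese they are, and no adiposity measure is among the named covariates. A T2DM association could then partly reflect adiposity within the obese range.

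**Working it through.** No figure in the plan settles this point. The Phase 1 sample size of 80 concerns power, not which contrast is estimable. The check is to list the groups and see which differences they identify.

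**1. Cells of the obesity-by-diabetes table**

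| | No T2DM | T2DM |
|---|---|---|
| Not obese | none planned | none planned |
| Obese (BMI ≥ 25) | 40 | 40 |

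Sources: Sections 2.3.3 and 2.3.5, and the Abstract. Two of the four cells are filled.

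**2. Contrasts.** Write m(O,D) for the mean outcome, with O = 1 if obese and D = 1 if diabetic.

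- T2DM within obesity: b = m(1,1) − m(1,0). Both means are observed, so b is estimable.
- Obesity without T2DM: a = m(1,0) − m(0,0). The second mean is not observed, so a is not estimable.
- Combined condition against neither: m(1,1) − m(0,0) = a + b. Not estimable, because a is missing.

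**3. Can another phase supply the missing cell?** Phase 2 develops and validates the yoga module. Phase 3 (Sections 2.5.2 and 2.5.3) is a pre-post study in people recruited in Phase 1. Neither adds a non-obese group.

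**4. Direction of the gap.** The combined difference is a + b, and Phase 1 shows b. The documents give no value for a. Suppose, purely for illustration, that b = 0.5 SD:

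- a = 0.2: combined 0.2 + 0.5 = 0.7 SD, so b is smaller than the combined difference.
- a = 0: combined 0.5 SD, so b equals it.
- a = −0.2: combined −0.2 + 0.5 = 0.3 SD, so b is larger.

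The contrast falls short of the combined difference only if a is positive. Sections 1 and 5 of the article argue from that premise, but Phase 1 cannot test it. The Introduction also allows that the two conditions amplify each other (said there of cognitive impairment and dementia risk). In that case b already contains the interaction, and no fixed split between the two conditions applies.

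**5. Adiposity within the obese range.** Section 2.3.6.2 measures BMI and waist circumference. Section 2.3.6.7 names four covariates: age, sex, education and physical activity. Assume a model on all 80 participants with an intercept, a T2DM term and these four covariates, each taking one parameter. Residual degrees of freedom are 80 − 6 = 74. Adding BMI or waist leaves 80 − 7 = 73.

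**The case against.** The strongest defence is that nothing in the formal plan is wrong. The sentence in Section 5 is about the whole three-phase study, not Phase 1. The Phase 1 objective, groups, eligibility and two-group analysis agree with one another. Restricting both groups to obese adults is a legitimate way to isolate T2DM. The article also often uses obesity and T2DM together as a name for its target population, so the sentence can be read as saying who is studied rather than which effects are separated.

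Most of this stands. A reader might infer that the Phase 1 objective or analysis is faulty; the documents do not support that. It does not rescue the broad sentence, because no phase contains the reference that an association with obesity would need, and the limitations give no warning.

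A reader might also infer that Phase 1 understates the burden of the combined condition, and want a percentage. The documents do not support that either. They never offer the group difference as an estimate of combined burden. The direction depends on an unknown obesity effect, and any percentage would only restate an assumed ratio.

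On the covariate, one may say that BMI could be among the metabolic indices in Section 2.3.6.7, or be left to an analysis plan. That is possible. But the article does list its adjustment variables, and adiposity is not among them. Adjusting for BMI or waist describes a gradient among obese people and does not replace a non-obese group.

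**Conclusion.** The concern holds as a mismatch between claim and design, together with an unstated limitation. The purpose in Section 5 and the burden wording in the Abstract are wider than anything the three phases can estimate. What can be estimated is the difference associated with T2DM among elderly adults with BMI of at least 25.

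This conclusion rests only on the eligibility criterion, the two groups and the absence of any other group in later phases. It needs no numerical assumption. That the contrast leaves out an obesity contribution depends on obesity itself affecting these outcomes, which the Introduction presumes and the study cannot check. The size of the omission is not computable from the documents.

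The Phase 1 objective and group comparison can stay as they are. The matter is worth correcting now because the article states that no participant data have been collected.

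**What to change.** 1. In Section 5, and where the Abstract speaks of disease burden, restate the between-group claim as differences associated with T2DM among elderly adults with obesity, in line with Section 2.3.1.
2. Add a limitation to Section 5: Phase 1 has no non-obese or metabolically healthy reference, so it estimates neither the obesity association across that divide nor the combined burden, and a null group difference is not evidence of an unaffected brain.
3. Add BMI or waist circumference to the regression covariates in Section 2.3.6.7, so that T2DM associations are separated from differences in adiposity within the obese range.

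The first two items cost wording and a narrower stated claim. The third uses data already planned and costs one degree of freedom per model. No new group or assessment is required.

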## Ethical considerations

The study will be conducted in strict accordance with the Declaration of Helsinki and ICMR’s National Ethical Guidelines for Biomedical and Health Research Involving Human Participants. IEC approval was obtained from the Institutional Ethics Committee, Kasturba Hospital, Manipal (IEC1: 520/2025). All participants will receive oral and written explanations of the study purpose, procedures, risks, benefits, confidentiality safeguards, and their right to withdraw at any time without affecting their clinical care. Signed written informed consent will be obtained.

## Data Availability

No data are associated with this article. This is a study protocol; no participant data have been collected at the time of publication. This protocol has been prepared in accordance with the Standard Protocol Items: Recommendations for Interventional Trials (SPIRIT 2025) guidelines. The completed SPIRIT 2013 checklist has been deposited in the Figshare repository. Repository name: An MR-Neuroimaging Study of Structural and Vascular Brain Networks in Elderly Adults with Obesity and Diabetes who Practice Structural Yoga.
https://doi.org/10.6084/m9.figshare.32151694.
^
37
^ License:
CC0 1.0 Universal (CC0 1.0) Public Domain Dedication. Clinical Trials Registry — India (CTRI): CTRI/2025/12/098738. Registered: 10/12/2025. URL:
https://ctri.nic.in/Clinicaltrials/pmaindet2.php?EncHid=MTQ4MTg5&Enc=36227.78897&userName=
